### The study instruments

#### 1Demographic information questionnaire

This questionnaire will include the couple's demographic information: age, education level, occupation, income, age at marriage, and duration of marriage. Additionally, information about a woman's fertility will include abortion, age at first menstruation, menstrual cycle regularity, and possible prevention methods. This questionnaire will only be completed in person at the beginning of the study.

#### Level of knowledge

The questions in this section are based on the material taught in the training sessions and are designed to investigate changes in the level of awareness of participants, as increasing the awareness of couples can help them make better decisions in the field of reproduction [29].

#### Trans-theoretical model questionnaire (TTM)

At the beginning of the study, to find out whether the person meets the criteria to enter the study or not, the participant must fill out a questionnaire about the stages of change, and whether they are in the pre-contemplation or contemplation stage, it is included in the study. This questionnaire is designed based on the stages of the change model and includes 7 questions to determine which stage the person is in. After the intervention, each participant's level of change toward the next steps in behavioral intentions will be measured using this questionnaire according to specific steps.

#### Theory of planning behavior questionnaire (TPB)

The next questionnaire developed by the researchers will be based on the theory of planned behavior. According to this theory, human behavior is directly determined by three main factors: attitudes, subjective norms, and perceived behavioral control [27]. Therefore, the designed questionnaire will also have three parts. 15 questions will measure individual attitudes, 10 questions will measure subjective norms and 25 questions will measure perceived behavioral control of the couples. Due to the influence of different environmental factors on the "Perceived behavioral control" factor, questions related to economic issues (6 questions), employment and work-related factors (5 questions), educational factors (2 questions), social factors (6 questions), questions about physical factors (3 questions) and mental factors (3 questions) are designed separately.

### Validity and reliability

In this study, three questions need to be tested for validity and reliability:

Knowledge level, TTM, and TPB. The reliability of the questions will be determined by its internal consistency (Cronbach's alpha) and the content validity of the questions will be assessed using both qualitative and quantitative methods. In the qualitative method, 10 experts evaluate the questionnaire, including faculty members of the Department of Midwifery and Reproductive Health of Tehran University of Medical Sciences, and after receiving their opinions, the proposed changes will be applied. The Content Validity Index (CVI) and Content Validity Ratio (CVR) are measured quantitatively. For face validity, we ask 10 couples to give comments on the clarity of the survey, and based on their opinions, basic explanations are given, if the survey is unclear from the couple's point of view, the necessary corrections will be performed.

### Sample size

To provide a power of 95% with a 99% confidence interval using the following formula and considering the mean and standard deviation of intention to have based on the findings of a similar study by Moghaddam et al. [36]. The sample size was estimated at 12, and then considering 20% attrition, we plan to recruit 15 couples per group and a total of 30 couples study participants.$$n=\frac{{( {z}_{1-\frac{\alpha }{2}}+ {z}_{1-\beta } )}^{2} ({s}_{1}^{2}+ {s}_{2}^{2})}{{({\mu }_{1}- {\mu }_{2})}^{2}}=\frac{2.1664 \times 14.82}{2.6896}=\frac{32.106048}{2.6896}=11.93 \cong 12$$

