### Statistical analysis

The analytical method used in this study will be quantitative. The information recorded in the questionnaire will be entered into the SPSS program at each stage and data analysis will be conducted after the research process is completed. Categorical variables will be reported based on frequency, and quantitative variables will be reported as mean (SD). The ANOVA test will be used for quantitative variables that have a normal distribution, and the Friedman test will be used for quantitative variables that do not have a normal distribution. The effectiveness of the intervention will be determined using an ANOVA test and the impact of demographic variables on factors measured using a logistic regression model. Statistical analyses will be performed using IBM-SPSS 22. For all analyses, P values  < 0.05 are considered statistically significant.

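### The sample-size calculation uses the multiplier for 90% power, not the stated 95%, and is sized at alpha 0.01 while the analysis tests at 0.05

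*Protocol article*

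**What the plan says.** The Sample size section of the protocol article introduces its calculation with "To provide a power of 95% with a 99% confidence interval using the following formula". It prints the usual two-means formula: the squared sum of z at 1 − α/2 and z at 1 − β, times the sum of the two variances, divided by the squared difference in means. The means and SDs of intention are taken from a similar published study, but the values themselves are not given.

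The worked line is 2.1664 × 14.82 / 2.6896 = 32.106048 / 2.6896 = 11.93, taken as 12. Nothing says which numerator factor is the z-term and which is the variance sum. The section concludes: "The sample size was estimated at 12, and then considering 20% attrition, we plan to recruit 15 couples per group".

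The Statistical analysis section sets a different level. For all analyses, P values "< 0.05 are considered statistically significant".

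**The concern.** A stated alpha and power fix the z-term completely, so it can be checked without the source study. The z-term for 99% confidence and 95% power does not appear in the worked line. The level used for sizing is also not the level used for testing, and no reason is given.

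This is the trial's only sample-size justification. A reader who relies on it will take the trial to have 95% power for a test at 0.01. The calculation does not deliver that power, and the test at that level is not the one planned.

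**Working it through.** **Inputs** (Sample size section unless noted)
- Stated power 95%: z = 1.645.
- Stated confidence 99%: alpha 0.01. The formula uses z at 1 − α/2, so the test is two-sided and z = 2.576.
- Numerator factors: 2.1664 and 14.82, unlabelled.
- Denominator: 2.6896 = 1.64², so the difference in means is 1.64.
- Allocation 1:1; attrition 20%.
- Test level 0.05 (Statistical analysis section).

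**1. The printed arithmetic reproduces.** 2.1664 × 14.82 / 2.6896 = 11.937, rounded up to 12; 12 / 0.8 = 15.

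**2. The stated targets do not give that line.** The required multiplier is (2.576 + 1.645)² = 17.81. Neither factor equals it.

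**3. What 14.82 is.** (2.57 + 1.28)² = 3.85² = 14.8225, which is two-sided alpha 0.01 with 90% power using shortened z-values (14.88 unrounded). Other pairings do not match:
- two-sided 0.05 with 95% power: 12.99
- two-sided 0.05 with 99% power: 18.37
- one-sided 0.01 with 95% power: 15.77

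**4. Reading A: 14.82 is the z-term and 2.1664 the variance sum.** The common SD is √(2.1664/2) = 1.041 and the standardised difference is 1.64 / 1.041 = 1.58.

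| Couples per group | Alpha | Power, protocol's formula | Power, t-test |
|---|---|---|---|
| 12 | 0.01 | 90.0% | 83.9% |
| 12 | 0.05 | 97.1% | 95.8% |
| 15 (no attrition) | 0.01 | 95.9% | 93.0% |
| 15 (no attrition) | 0.05 | 99.1% | 98.6% |

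Size needed for 95% power at two-sided 0.01:
- Formula: 17.81 × 2.1664 / 2.6896 = 14.35, so 15 evaluable. With attrition, 15 / 0.8 = 18.75, so 19 per group (38 in total, against 30 planned).
- t-test: 16.1, so 17 evaluable.

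Size needed for 95% power at two-sided 0.05, by the formula: 12.995 × 2.1664 / 2.6896 = 10.47, so 11 evaluable. With attrition, 11 / 0.8 = 13.75, so 14 per group.

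**5. Reading B: factors in printed order, so 2.1664 is the z-term and 14.82 the variance sum.** The two z-values would sum to √2.1664 = 1.47, below 2.576 alone. The standardised difference is 1.64 / √(14.82/2) = 0.60.
- Power with 12 per group at 0.01: about 14% (formula) or 11% (t-test).
- Power with 12 per group at 0.05: about 31% (formula) or 29% (t-test).
- Size for 95% power at 0.01: 17.81 × 14.82 / 2.6896 = 98.1, so 99 per group.

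Neither reading gives 95% power at alpha 0.01 with 12 per group.

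**The case against.** The strongest reply is that the trial will test at 0.05. There, on the likely reading, 12 per group gives 97.1% power by the formula and 95.8% by t-test, so the stated 95% is met at the level that counts. Sizing at 0.01 is the conservative direction: it costs no power and leaves the type I error of the planned tests alone. This stands, and it limits the consequence. It does not make the Sample size statement true, because that statement ties the 95% to 99% confidence.

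A second reply is that Reading B is implausible and its low power figures should carry little weight. That is largely right: 14.82 matches 3.85² closely, no usual design has z-values summing to 1.47, and swapping two factors in a product changes nothing. Reading A is still an inference, because the means and SDs behind the factors are not printed. Reading B is a reason to label them, not evidence that the trial has 30% power.

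Third, the t-test figures go beyond the protocol's own method. That is fair. By its own formula the shortfall is 90% against 95%, or 12 against 15 evaluable couples, and the finding holds on those figures alone.

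Finally, any restated power concerns mean intention. The Primary outcome section names stage change and attitude, so the corrected sentence should not be read as covering those.

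**Conclusion.** The concern holds. The calculation used the multiplier for 90% power at two-sided alpha 0.01 and reported the result as 95%. By the protocol's own formula the error is 5 percentage points of power, 3 evaluable couples per group (12 against 15) and 4 recruited couples per group (15 against 19). Rounding cannot explain it: shortened z-values move 14.88 to 14.82, not 17.81 to 14.82. Recruiting 15 does not rescue the claim, because the extra three couples are the attrition allowance.

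Separately, sizing at 0.01 and testing at 0.05 conflict without explanation. On Reading A the trial is not underpowered at 0.05 for the assumed effect.

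These sizes assume that 14.82 is the z-term, that the two SDs are equal (for the t-test figures), and that the unseen difference and SDs were transcribed correctly. That the stated power is wrong does not depend on which factor is which.

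**What to change.** 1. Check against the source study which factor is the variance sum. Print the two SDs, the two means and the two z-values, each labelled and in the order of the formula.
2. Use the same alpha in the Sample size and Statistical analysis sections.
3. Restate the power to match. If Reading A is confirmed and 0.05 is kept, for example: 12 evaluable couples per arm give about 96% power (t-test) at two-sided alpha 0.05 for the assumed difference in mean intention. If 0.01 is kept, state about 90% by the formula or 84% by t-test. If Reading B proves correct, state roughly 30% at 0.05.

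This is a wording correction with no added couples, though the stated figure may become less favourable. Only if the sponsor wants to keep both 95% power and alpha 0.01 does enrolment change, to 19 per group by the protocol's formula.

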### Randomization

After checking the participants' basic information regarding the inclusion criteria, a list will be prepared, and then, to randomly divide them into two intervention and control groups, samples will be allocated into two groups based on the Random Number Table. Because interventions aim to educate people, participants cannot be blinded. The people targeted by the intervention are therefore aware of the group to which they belong.

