**Methods:**

Thirty couples (intervention, n = 15; control, n = 15) will be enrolled in this cluster randomized controlled trial. After collecting baseline data and separating participants in the pre-contemplation and contemplation stages based on the TTM, the samples were randomly assigned to the intervention and control groups. The intervention group will receive 60-min training based on TPB components for 4 weeks. The first follow-up assessment was performed immediately after the intervention and the final assessment 6 months later. For all 3 time assessments, three questionnaires will be used: The knowledge questionnaire, the TTM, and the TPB questionnaire. The most important consequences are changes in knowledge, attitudes, subjective norms, perceived behavioral control, and stages of intentions to have children.

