3	Addressing the role of perceived behavioral control in childbearing	PowerPoint Pamphlet of the third session Video	1) Review of previous session (5 min) 2) Giving information on requirements and cares for becoming pregnant, prenatal cares, and care of newborn (30 min) 3) Presenting a short video which shows how a baby develops (5 min) Showing how to provide care during pregnancy and for newborn (10 min) 4) Showing videos of care of newborn (10 min) 5) Question and answer (10 min)
4	Addressing the behavioral intention and explaining how childbearing will change couple’s life	PowerPoint Pamphlet of the fourth session Video	1) Reviewing previous session (5 min) 2) Giving information on advantages of having a child from cultural, religious and social perspectives (10 min) 3) Showing videos of successful childbearing expression (10 min) 4) Question and answer (10 min)

Participants who meet the inclusion criteria will first complete a childbearing intentions questionnaire, which will be designed based on the stages of the change model and the samples who are in the pre-contemplation and contemplation stage will be included in the study. After this step, by accessing the Sib system “a national system that records health information of individuals”, couples who have been married for 2 years without children and meet the inclusion criteria will be selected. Then, 60 samples (30 pairs) will be selected through a random number table and will be randomly divided into 2 groups: control and intervention.

Teaching methods will include conferences, discussions, Q&A, and document distribution. During the classes, the researcher does not impose personal views and attitudes on the couple. It is explained to them that all decisions about having children are based entirely on their opinions and considerations and there is no coercion. They must also fill in the questionnaires without concern and honesty because their answers do not affect the quantity and quality of the treatment, and whenever they do not want to participate in the study, they can refuse to continue.

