### Blinding

Additionally, there was no possibility of blinding the researcher due to the organization of the training sessions and the conduct of the interventions. However, medical center staff will be blinded. Blinding is also done when dividing the participants into two control and intervention groups and during the statistical analysis of the data. Training sessions for the intervention group will take place on days when people in the control group are not present at the clinic so that information is not randomly delivered to them and they do not communicate with each other. This issue will be the reason for the long process (about 2 years) of this research.

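### The abstract separates couples by entry stage before randomisation, but the body of the protocol divides one pool; reconcile the two and allocate within stage

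*Protocol article*

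**What the plan says.** The Abstract (Methods) gives this order: "After collecting baseline data and separating participants in the pre-contemplation and contemplation stages based on the TTM", and only then random assignment to the two groups.

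The body of the article describes something simpler. Under Interventions, people complete a stage questionnaire and those in either of the two early stages are admitted. Then "60 samples (30 pairs) will be selected through a random number table and will be randomly divided into 2 groups: control and intervention". Under Randomization, the order is "After checking the participants' basic information regarding the inclusion criteria, a list will be prepared, and then, to randomly divide them", and the rule is "samples will be allocated into two groups based on the Random Number Table". Neither section divides the couples by stage before allocating them. The Inclusion criteria and the description of the TTM questionnaire also use stage only to decide who may enter.

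The Sample size section fixes the arms: "we plan to recruit 15 couples per group and a total of 30 couples study participants". The Primary outcome section names movement of couples to the later TTM stages as a primary outcome, alongside a change to a positive attitude.

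**The concern.** A reader who follows the abstract would build two lists, one per stage, and randomise within each. A reader who follows the Interventions and Randomization sections would build one list and ignore stage. Both cannot be the procedure of the same trial.

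Stage is not an incidental covariate here. It is measured on everyone before allocation, and the primary outcome is counted from it. A couple that starts in contemplation is one stage nearer the target than a couple that starts in pre-contemplation. The Trial design section also frames the question as whether couples leave pre-contemplation, which only those who start there can do. With 15 couples per arm, a chance surplus of contemplation couples in one arm could look like an effect or hide one.

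The word used for the things allocated adds a smaller ambiguity. Interventions counts 60 samples as 30 pairs, and Randomization then allocates samples. The sample size in couples points to the couple as the unit, but the allocation rule does not say so.

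**Working it through.** **1. The passages side by side.**

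| Place | Role of stage | What is divided |
|---|---|---|
| Abstract, Methods | Separation by stage precedes assignment | Not said to be one pool |
| Interventions | Entry screen | 30 pairs, one pool |
| Randomization | Not mentioned | One prepared list |
| TTM questionnaire | Entry screen; later a measure of change | – |

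The abstract's separation can be read as stratification, or as the entry screen in other words. The body supports only the second. The text does not settle which is meant.

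**2. What ignoring stage would cost.**

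Inputs: 30 couples and 15 per arm (Sample size; Abstract). The number of couples m in a given entry stage is not stated, so m = 10, 12 and 15 are assumed. For this calculation each couple is taken to have a single stage.

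Rule evaluated: 15 of the 30 listed couples are drawn at random for one arm and the rest form the other. This is the reading most favourable to the protocol, because it gives 15:15 exactly.

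Let x be the number of stage couples in the first arm. Then P(x) = C(m, x) · C(30 − m, 15 − x) / C(30, 15), with C(30, 15) = 155,117,520. The between-arm difference is |2x − m|. The table gives the chance that it is 4 couples or more, doubling the lower tail by symmetry.

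| Assumed m | Splits counted | Lower-tail count | Probability |
|---|---|---|---|
| 15 | 10 v 5 or worse | 1 + 225 + 11,025 + 207,025 + 1,863,225 + 9,018,009 = 11,099,510 | 2 × 11,099,510 / 155,117,520 = 0.143 |
| 10 | 7 v 3 or worse | 15,504 + 387,600 + 3,488,400 + 15,116,400 = 19,007,904 | 2 × 19,007,904 / 155,117,520 = 0.245 |
| 12 | 8 v 4 or worse | 816 + 36,720 + 565,488 + 4,084,080 + 15,752,880 = 20,439,984 | 2 × 20,439,984 / 155,117,520 = 0.264 |

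By symmetry, m = 20 and m = 18 give the same values as 10 and 12. The result for 15 is lower partly because an odd m allows only odd differences, so "4 or more" there means 5 or more. A very uneven split gives less: m = 5 gives 6,537,520 / 155,117,520 = 0.042.

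**3. What allocating within stage would give.**

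An even stratum splits equally. An odd stratum leaves one couple over, so the arms differ by one there. With 15 couples in each stage the split is 8:7 in one and 7:8 in the other, and the total is still 15:15. Differences of 4 or more cannot occur.

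**The case against.** The strongest reply is that nothing is wrong with the stated randomisation. A finished list from which 15 of 30 couples are drawn by random number table is a valid method. The imbalances above are ordinary chance, already allowed for in the significance level. Separating by stage may simply be the abstract's phrase for the entry screen. Stratifying so small a trial is a preference, and a condensed article may leave strata to the full protocol.

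Much of this stands. The validity of the test is not in question, and the abstract's wording falls short of a commitment to stratify. The mere absence of strata from an article would be no finding. What remains is that the abstract and the body read differently on a step that must be carried out one way or the other, for a variable tied to a primary outcome and already in hand.

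Three stronger readings are tempting and are not supported:

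- *The arms will usually miss 15:15.* If each couple were assigned by an independent draw, exactly 15:15 would occur with probability C(30, 15) / 2^30 = 0.144. But the text describes 30 pairs selected and listed and then divided, which is compatible with drawing 15 of them.
- *The last couples' arm is known in advance.* That requires couples to be enrolled and assigned one after another until an arm is full. The document does not say this, and the Blinding section attributes the two-year duration to keeping sessions apart from control couples.
- *The stated blinding fails.* The protocol says "there was no possibility of blinding the researcher due to the organization of the training sessions" and also "Blinding is also done when dividing the participants into two control and intervention groups". The first concerns delivery of the sessions and the second concerns allocation, so both can be true. Who holds the sequence may be set out in the full protocol.

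**Conclusion.** The point holds in a limited form. The abstract and the Interventions and Randomization sections differ on whether couples are separated by stage before allocation, and they must be reconciled. If stage is ignored, the chance of a difference of 4 or more couples in one stage is about 0.14 to 0.26 for the splits examined, against none if allocation is balanced within stage.

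Those probabilities rest on an assumed stage split, on a 15-of-30 draw and on each couple having one stage. They measure avoidable chance imbalance. They are not evidence of bias, and a reader should not infer from them that the allocation is predictable, unconcealed or unable to reach 15:15.

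**What to change.** Use the same wording in the Abstract, Interventions and Randomization sections:

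1. The couple is the unit allocated.
2. Before allocation, define the stratum of a couple whose spouses are in different stages, since the questionnaire classifies each person. For example, use three strata: both pre-contemplation, both contemplation, mixed.
3. After all baseline forms are complete, give each couple a code, randomly permute the codes within each stratum and assign half to each arm. Assign the odd couples at random, subject to a total of 15:15.
4. Include the stratum in the analysis of the intervention effect.

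If allocation has already been made, as the abstract's past tense may suggest, state which procedure was used, report entry stage by arm and include it in the analysis.

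The cost is small: a stratum rule, a permuted list and a few sentences, with no extra couples or visits. The list must be prepared and held by someone who is neither the teaching researcher nor a person meant to stay blind, because whoever holds it knows the allocation.
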